##### Early Detection Cohort

We propose a cluster randomized study to be implemented at 18 HIV treatment facilities in Lusaka province. Three facilities serving each type of regional population (urban, periurban, or rural populations) will be randomly assigned to a study arm: the ARROW program or one-time education. Overall, 9 (50%) facilities will be assigned to each arm of the trial, with data collection at baseline and at 12-, 24-, and 36-month follow-up. At each of the 18 clinics, we will enroll 100 men and 100 females resulting in a total of 3600 participants in the early detection cohort. The 200 AYA living with HIV per facility will be selected by first reviewing the HIV register and identifying those who meet the study inclusion criteria: 15 to 39 years of age, on ART for at least 6 months, not pregnant, and with no pending plans to move from the current residence during the 3-year study duration. For all the 3600 participants, we will collect baseline data and capture information on study end points from the SmartCare system, and the supplemental data will be collected by PCs and trained study data collectors (eg, tracking referrals for all participants and obtaining results of biopsies).

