##### Cancer Treatment Cohort

This will take place entirely at the Cancer Diseases Hospital, with some patients being recruited from the University Teaching Hospital. A total of 500 AYA living with HIV who have been diagnosed with CC, NHL, or KS will be recruited into the study, with 50% (250/500) of the patients in each trial arm (ie, one-time educational campaign vs the ARROW intervention). Patients will be surveyed annually at 12, 24, and 36 months. Trained data collectors will obtain consent and enroll AYA living with HIV, aged 15 to 39 years. We will be aiming for the following targets for each cancer type: 50% (250/500) of the participants with CC, 30% (150/500) of the participants with KS, and 20% (100/500) participants with NHL (with an overall equal number of male and female AYA living with HIV for KS and NHL). While AYA living with HIV who are pregnant will be excluded, as they require specialized care, those who become pregnant during the trial period will remain enrolled in the study; CC screening and physical examinations for KS and NHL will be offered based on Zambian guidelines pertaining to pregnancy.

We hypothesize that, by facilitating peer support to address barriers and gaps at multiple levels, the ARROW program will be more effective than the one-time education campaign, but more expensive as well. As shown in Figure 2, we will simultaneously conduct separate randomized controlled trials at the HIV treatment facilities and at the Cancer Diseases Hospital. The trials will be initiated upon completion of the preimplementation preparation activities. We will then embed PCs into the care teams at the HIV facilities and the Cancer Diseases Hospital and initiate the planned implementation activities of the ARROW Provider Network in the ARROW program arm. The comparison arm will receive the one-time education campaign: health care providers at the HIV facilities (particularly physicians and nurses) will receive a brochure with key guidance for early diagnosis of cancers in AYA living with HIV, and the AYA living with HIV upon recruitment will also receive education brochures at both the HIV facilities and the Cancer Diseases Hospital. The Health Care Collaborative will continue to meet as planned on a quarterly basis.

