##### Cancer Treatment Cohort

We will use stratified random assignments to place patients in each arm of the trial. Once we have enrolled 10 patients with each type of cancer, we will randomly assign half to the ARROW program and the other half to the one-time education arm. All patients will have a minimum of 12 months of follow-up, and some will have up to 36 months of follow-up. Data will be collected at baseline and then annually for the 3-year duration of the trial from the AYA living with HIV through surveys and by abstracting information from the Cancer Diseases Hospital records. The sample size (n=500) was calculated using conventional specifications (α=.05; 2-sided tests) based on the primary end point and allowing for an absolute 15% point improvement; the estimated current level of adherence is 75%, which will increase to at least 90% with the ARROW program. With 50% (250/500) of the patients in each arm, we will have more than 90% power to detect this difference.

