### Analysis of Hypotheses

We will use an intent-to-treat approach to test the hypotheses (related to the dual primary and secondary end points) that AYA living HIV in the ARROW program, compared with those receiving one-time education, will have higher uptake of early diagnostic services, increased adherence to treatment, and improved outcomes.

For the facilities assigned to the intervention group in the early detection cohort, we will examine the effects at the individual level across the 2 randomization groups. Given the need to consider the influence of the cluster randomization, we will use generalized estimating equation models to estimate the effect across the trial arms. If the Hausman assumption of correlation between the random and fixed effects is violated, then we will include fixed effects representing cluster identification [74]. For the cancer treatment cohort, we will generate summary statistics for the end points and test statistical significance. We will also conduct logistic regressions to identify key factors that predict adherence.

For both trials, we will adjust for baseline covariates, including sociodemographic factors, should the initial descriptive analyses suggest differences in the distribution of these factors across the study arms. We will also explore the use of propensity scores to control for systematic differences between the AYA living with HIV in the 2 trial arms. In further analyses, we will compare differences in mediating outcomes across the randomized groups and examine the potential moderating roles of key individual behavioral and social factors hypothesized to influence adherence along the cancer care continuum (eg, social support, stigma, and self-efficacy), as shown in Figure 1. We will test the “dose” of the ARROW program received as a covariate in these models. In additional analysis, we will explore differences in the end points by age groups and type of cancer, as appropriate. We will also assess whether knowledge, self-efficacy, social support, and stigma differ by age groups and among AYA living HIV, both with and without cancer.

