### Limitations and Approaches to Minimize Bias

First, although cluster randomization reduces contamination across study arms, it increases the risk that the AYA living with HIV in each arm may differ at baseline. The study sampling frame, based on the HIV registers, will allow us to assess baseline differences before facility randomization and adjust our sampling process with propensity score weights. Second, data could be missing because of nonresponse and study attrition. The PCs will maintain regular contact with the AYA living with HIV, and we will use rigorous field data collection practices, including training data collectors, developing protocols, and monitoring fidelity continually. Furthermore, we will address any missing data by including demographic covariates that will serve as proxies for dropout and conducting sensitivity analyses. Third, we anticipate health care provider turnover at the HIV treatment facilities and will conduct refresher training sessions as needed throughout the trial period.

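### Covariate adjustment is triggered by observed differences between arms, so the primary model is not fixed in advance and the trigger would pass over the randomisation strata

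*Protocol article*

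**What the plan says.** Only the protocol article is at hand.

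- **Adjustment rule, both trials (Analysis of Hypotheses):** "we will adjust for baseline covariates, including sociodemographic factors, should the initial descriptive analyses suggest differences in the distribution of these factors". The list of covariates is open and no threshold is given. The next sentence adds: "We will also explore the use of propensity scores to control for systematic differences".
- **Stated analyses (same section):** generalised estimating equations for the early detection cohort; summary statistics and an unnamed significance test for the cancer treatment cohort. Neither names a stratification factor. Cancer type appears only among additional exploratory comparisons.
- **Design, early detection cohort (Overall Study Design):** "Three facilities serving each type of regional population (urban, periurban, or rural populations) will be randomly assigned to a study arm". Region type is thus balanced at three facilities per type per arm.
- **Design, cancer treatment cohort (Sample Size and Recruitment):** "We will use stratified random assignments to place patients in each arm of the trial", and "Once we have enrolled 10 patients with each type of cancer, we will randomly assign half to the ARROW program". Cancer type is thus balanced in blocks of 10. The target mix is "50% (250/500) of the participants with CC, 30% (150/500) of the participants with KS, and 20% (100/500) participants with NHL".
- **Limitations and Approaches to Minimize Bias:** the HIV registers "will allow us to assess baseline differences before facility randomization and adjust our sampling process with propensity score weights".

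**The concern.** Two things go wrong with an imbalance trigger.

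First, the choice among an unadjusted, an adjusted and a propensity-score estimate waits until the arms have been compared. With nine facilities per arm, chance differences at facility level are common, so the trigger will often have something to act on.

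Second, it selects on the wrong property. A covariate earns its place in the model by predicting the outcome or by having been used in the randomisation, not by looking uneven. Region type and cancer type were made even on purpose, so a search for differences should not find them. If they are left out and they do predict the outcome, their variance stays in the error term. Precision is then lost that the design had already secured.

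The Limitations text adds a third difficulty. It gives propensity scores a different job, at a time when no arms exist.

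**Working it through.** **1. The article's own power figures.** Inputs from Sample Size and Recruitment and Overall Study Design: 9 facilities per arm; 200 participants each (100 female), less 10% attrition, so m = 180 (examination) or 90 (CC screening); two-sided α = 0.025; intraclass correlation (ICC) 0.03 to 0.05. The design effect is 1 + (m − 1)·ICC.

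- Examination, ICC 0.05: 1 + 179 × 0.05 = 9.95; effective n per arm = 9 × 180 / 9.95 = 162.8. Power for 15% v 35%: 97.6% (normal), 95.5% (noncentral t, 16 df).
- CC screening, ICC 0.05: 1 + 89 × 0.05 = 5.45; effective n = 9 × 90 / 5.45 = 148.6. Power for 20% v 40%: 94.0% (normal), 90.4% (t, 16 df).
- ICC 0.03 (normal): 99.9% and 99.2%.
- Cancer treatment cohort, 250 per arm, 75% v 90%, α = 0.05: 99.4%.

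The stated figures (over 90%, over 85%, over 90%) are reproduced without any stratification.

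**2. The trigger.** The article sets no threshold, so assume p < 0.05 on five independent covariates. The chance that at least one fires under pure randomisation is 1 − 0.95⁵ = 22.6% (simulation: 22%). At p < 0.20 it is 1 − 0.80⁵ = 67.2% (simulation: 66%). In simulations with 18 clusters and covariates explaining 30% to 50% of the variance of cluster means, firing moves the estimate by 0.33 to 0.39 SD of those means. Followed mechanically, the rule has type I error 0.012 to 0.020 against 0.025. Taking the best of the unadjusted, rule-based and fully adjusted results gives 0.043 to 0.046.

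**3. Omitting region type.** Assumptions: uptake 15%, ICC 0.05, m = 180, and region explaining a fraction f of between-facility variance.

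- Between-facility variance: 0.05 × 0.15 × 0.85 = 0.006375.
- Sampling variance of a facility proportion: 0.95 × 0.1275 / 180 = 0.000673.
- Stratified variance per facility: (1 − f) × 0.006375 + 0.000673.
- Unstratified: the same plus (9/8) × f × 0.006375. The factor 9/8 arises because three fixed regions are spread over nine facilities and the sample variance divides by 8.

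| f | Stratified | Unstratified | SE ratio |
|---|---|---|---|
| 0 | 0.007048 | 0.007048 | 1.00 |
| 0.25 | 0.005454 | 0.007247 | √0.753 = 0.87 |
| 0.50 | 0.003860 | 0.007446 | √0.518 = 0.72 |

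The unstratified t test has critical value 2.473 (16 df). On the correct scale this is 2.473 / 0.868 = 2.85 for f = 0.25 and 2.473 / 0.720 = 3.43 for f = 0.50. The two-sided t tails are about 1.2% and 0.3% against the nominal 2.5%, and simulation agrees.

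**4. What that does to power.** Simulated cluster-level analyses, 3 regions × 3 facilities × 2 arms, ICC 0.05; unstratified (16 df) → stratified (12 df), with between-facility variance held at its control-arm value:

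| Effect | f = 0 | f = 0.25 | f = 0.50 |
|---|---|---|---|
| Examination 15% v 35% | 98.1 → 97.5% | 99.1 → 99.4% | 99.7 → 99.9% |
| CC screening 20% v 40% | 93.7 → 92.3% | 95.2 → 96.8% | 97.2 → 99.3% |
| Examination 15% v 25% (half the planned effect) | 53 → 51% | 51 → 61% | 50 → 77% |

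If ICC 0.05 instead applies at each arm's own rate, the last row becomes 44 → 42%, 42 → 53% and 39 → 69%. The largest gain at a 20-point effect is then about 5 points (CC screening, f = 0.50: 93.7 → 98.5%) rather than about 2.

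**5. Omitting cancer type.** Assume adherence of 85%, 70% and 57.5% for CC, KS and NHL, which averages 0.5 × 85 + 0.3 × 70 + 0.2 × 57.5 = 75%.

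- Unstratified SE: √(2 × 0.75 × 0.25 / 250) = 0.0387.
- Mean within-type variance: 0.5 × 0.1275 + 0.3 × 0.21 + 0.2 × 0.2444 = 0.1756; stratified SE: √(2 × 0.1756 / 250) = 0.0375.
- Simulated type I error: 0.042 v 0.050. Power for a 10-point effect: 81.4% v 83.3%.

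**6. The two uses of propensity scores.** A propensity score models arm membership, so it cannot be formed before facilities have arms. The Results section reports that early detection recruitment closed in February 2025, so the sampling can no longer be changed. Weighting the enrolled participants remains possible, but that is an analysis choice and falls under the rule in Analysis of Hypotheses.

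**The case against.** The strongest reply is that the article is condensed. It names a class of model without listing terms, does not exclude region or cancer type, and exact model terms usually belong in the analysis plan. That stands for the silence on strata taken alone. It does not cover the trigger, which is a stated commitment and which a later plan would have to overturn.

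It is also fair that the rule, followed mechanically, errs on the conservative side. Inflation needs an analyst who picks among results, and nothing in the article proposes that. What remains is that the primary estimate is not determined in advance.

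Three stronger readings are tempting, and the documents do not support them:

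- A reader might infer that the standard errors are wrong in general. They are too large only if the strata are prognostic, and the article gives no uptake by region or adherence by cancer type.
- A reader might infer that the trial is underpowered. The large gains in step 4 belong to 15% v 25%, half the difference that the article takes as its minimum for success.
- A reader might infer that a propensity model would separate the arms completely with so few facilities. That would need facility-level predictors. The article speaks of differences between participants and proposes no such model.

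**Conclusion.** The point holds in a limited form and should be corrected. Adjustment that depends on observed imbalance, with propensity scores in reserve, leaves the primary model open until baseline data are seen by arm. The same rule would not be expected to select the two factors that the randomisation used.

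The consequence is lost precision, not bias in the risk difference. For region type it ranges from nothing to a standard error that could be 13% to 28% smaller, under the assumed ICC of 0.05 and up to half of between-facility variance explained. For cancer type it is small (SE 0.0387 v 0.0375 under the assumed adherence rates). The stated power stands; the benefit is narrower intervals and more power for effects smaller than planned.

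These sizes come from cluster-level t tests standing in for the estimating-equation model. An uncorrected robust standard error with 18 facilities has its own small-sample error in the opposite direction, which is a separate matter.

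**What to change.** Delete the imbalance trigger and fix one primary model per cohort before any outcome is seen by arm. The article expected 12-month results in early 2026.

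- **Early detection cohort:** estimating equations or a cluster-level analysis with region type and age group (15–19, 20–24, 25–39), plus sex for the examination end point.
- **CC screening:** add baseline up-to-date status only if it can be taken from clinical records. Table 2 sets a two-year screening interval, so a pre-trial screen may still count at 12 months, but the table lists no baseline measurement of it.
- **Cancer treatment cohort:** a Mantel-Haenszel or logistic analysis stratified by cancer type.
- **Effect measure:** name it. Adding covariates to a logistic model changes what its odds ratio estimates, and the targets are in percentage points, so a standardised risk difference fits them.
- **Propensity scores:** label them as sensitivity analyses, and reconcile the Limitations text ("adjust our sampling process with propensity score weights") with Analysis of Hypotheses.

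The cost is mainly wording. Region type, sex, age group and cancer type already define the sampling or assignment. The between-facility degrees of freedom fall from 16 to about 12 to 14, which costs about 1 to 2 points of power at the planned effect if region is not prognostic.

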### Data Collection

In the HIV treatment facilities, we will generate electronic data files for the study cohort, and in other settings, such as referral facilities and the Cancer Diseases Hospital, the study team will abstract data from electronic databases or paper files. We will also conduct surveys to collect data from the AYA living with HIV and health care providers. The PCs will document their interaction with the AYA living HIV in the PC tracking tool, and the health care provider participation in the ARROW Provider Network will be captured in the study database. These details will be used to determine the “dose” of the ARROW program. All data will be collected by trained data collectors, who will undergo continual monitoring, and study coordinators, who will confirm fidelity to protocol specifications by random in-person review. Refer to Table 2 for the end point definitions and the biological, self-report, and clinical records data collected at baseline and at 12-, 24-, and 36-month follow-ups.

**Table 2 table2:** Data collection at baseline and at 12-, 24-, and 36-month follow-ups.

Constructs and measures		Instrument and specification	Source	Timing

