**HIV status, demographics, mediating outcomes, intervention dose, and clinical services**				
	HIV status and diagnosis date	Perinatally or behaviorally infected; CD4 count	Clinic record	Baseline
	Demographics and socioeconomic status	Research Triangle Institute AYA Zambia survey	Self-report	Baseline
	Self-efficacy (AYA living with HIV)	Generalized self-efficacy Scale [69]	Self-report	Baseline and 12, 24, and 36 mo
	Social support and mental health (AYA living with HIV)	Brief social support and patient health questionnaires [69,70]	Self-report	Baseline and 12, 24, and 36 mo
	HIV and cancer stigma (AYA living with HIV)	Anticipated stigma measures [71,72]	Self-report	Baseline and 12, 24, and 36 mo
	Cancer risk (AYA living with HIV)	Updated Research Triangle Institute cancer survey	Self-report	Baseline and 12, 24, and 36 mo
	Group education and sessions (AYA living with HIV)	Number and proportion of education sessions attended (dose)	PC tool; study database	12, 24, and 36 mo
	One-on-one education (AYA living with HIV)	Number of women receiving each level of strategy (dose)	PC tool; study database	12, 24, and 36 mo
	HIV and cancer team training (health care provider)	Proportion who attended initial training sessions (dose)	PC tool; study database	12, 24, and 36 mo
	Network meetings (health care provider)	Number and proportion of meetings attended (dose)	PC tool; study database	12, 24, and 36 mo
	Clinical team knowledge, confidence in ability, and collaboration (health care providers)	Survey on skills and patient communication; stigma related to AYA living with HIV (modified Nyblade instrument [73]) and peer learning and coordination	Self-report	Baseline and annually
	Diagnostic procedures by cancer type	Number of supplemental and diagnostic tests conducted	Clinical record	12, 24, and 36 mo
	Treatment modality by cancer type	Chemotherapy sessions; surgery; type of radiation	Clinical record	12, 24, and 36 mo

^a^KS: Kaposi sarcoma.

^b^NHL: non-Hodgkin lymphoma.

^c^CC: cervical cancer.

^d^PC: peer counselor.

^e^CD4: cluster of differentiation 4.

^f^Among AYA living with HIV and diagnosed with cancer.

^g^NHL stage based on the Lugano classification, CC stage based on the International Federation of Gynecology and Obstetrics, and KS stage based on the AIDS Clinical Trial Group system.

^h^AYA: adolescents and young adults.

^i^ART: antiretroviral therapy.

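### The further analyses adjust between-arm models for the ARROW dose received, a post-randomisation variable, so the arm coefficient in those models is not the programme effect

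*Protocol article*

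**What the plan says.** Analysis of Hypotheses in the protocol article has two layers. The confirmatory layer comes first: "We will use an intent-to-treat approach to test the hypotheses (related to the dual primary and secondary end points". It uses generalized estimating equations for the cluster trial, and dose is not mentioned there. A later paragraph adds a second layer: "In further analyses, we will compare differences in mediating outcomes across the randomized groups". That layer also examines whether social support, stigma and self-efficacy moderate adherence along the care continuum. The next sentence says the plan will test the dose "of the ARROW program received as a covariate in these models".

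Data Collection and Table 2 define dose. For participants, Table 2 lists "Number and proportion of education sessions attended (dose" for group education, recorded at 12, 24 and 36 months. For one-on-one education it lists "Number of women receiving each level of strategy (dose". The source is the peer counselors' log: "The PCs will document their interaction with the AYA living HIV in the PC tracking tool". A provider-level part is added: "health care provider participation in the ARROW Provider Network will be captured in the study database".

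The Individual Level section places the group sessions at ARROW facilities. The design section on the Cancer Treatment Cohort says that the comparison arm receives brochures.

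**The concern.** The further models compare the arms, yet they are to be adjusted for something that happens after randomisation and, at participant level, can happen only under ARROW. The protocol neither restricts the dose models to the ARROW arm nor names a method for a post-randomisation exposure.

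Two readings of the output would then go wrong. The arm coefficient could be taken as the programme's effect on a mediating outcome, when it describes ARROW participants who received no dose. The dose coefficient could be taken as evidence that more contact works, when people who are already engaged may both attend more and do better. What is at stake is the account of mechanism and moderation, not the test of whether ARROW works.

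**Working it through.** The protocol gives no figure for the dose analysis, so there is none to reproduce. Its power figures concern the arm comparison without dose and do not change.

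**Step 1: what the arm coefficient estimates.** Let A = 1 for ARROW and 0 for control, and let D be dose, with D = 0 in controls. Fit Y = a + bA + cD by least squares with no other covariates. Then:

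- a = control mean
- c = slope of Y on D within the ARROW arm, because controls have no variation in D
- b = (ARROW mean − control mean) − c × mean dose in ARROW

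The bracket is the total programme effect T, so b = T − c × mean dose. With a logit link the identity is no longer exact, but b still refers to ARROW at zero dose.

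**Step 2: without self-selection.** If a share s of T runs linearly through dose, then c × mean dose = sT and b = (1 − s)T. For s = 0, 0.5 and 1, b is T, 0.5T and 0.

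**Step 3: with self-selection.** If prior motivation raises both attendance and outcome, c is too large by some k > 0, and b falls by a further k × mean dose. For a programme with no effect (T = 0), b = −k × mean dose, which is negative, while c = k is positive.

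**Step 4: simulation as a check.** From the protocol: 18 facilities; 180 participants each (200 less 10% attrition); a 15% control rate and a 20-point effect (Sample Size and Recruitment, physical examination). The last two serve only as a convenient scale. Assumed: ICC about 0.04, inside the protocol's 0.03 to 0.05; dose from 0 to 6 sessions with mean 3; and, where self-selection is present, one SD of motivation adding 1 to the log-odds of attending and 0.03 to the outcome probability. There were 400 runs per row, each fitting a linear probability model.

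| Share of effect through dose | Self-selection | Arm, no dose in model | Arm, dose in model | Dose, per session |
|---|---|---|---|---|
| All | No | 0.1995 | −0.0003 | 0.0666 |
| All | Yes | 0.1994 | −0.0406 | 0.0800 |
| Half | No | 0.1988 | 0.0985 | 0.0334 |
| Half | Yes | 0.2000 | 0.0619 | 0.0461 |
| None | No | 0.2012 | 0.2032 | −0.0007 |
| None | Yes | 0.2033 | 0.1624 | 0.0136 |
| Null programme | No | −0.0028 | −0.0024 | −0.0001 |
| Null programme | Yes | −0.0004 | −0.0384 | 0.0127 |

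The second row confirms the identity in Step 1: 0.1994 − 3 × 0.0800 = −0.0406. Without dose, the arm coefficient recovers the simulated effect in every row. With dose it ranges from −0.04 to 0.20 for the same true effect of 0.20. A null programme with self-selection shows a spurious dose slope of about 0.013 per session.

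**The case against.** Several points on the other side are sound.

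- **The confirmatory analysis is separate.** A reader might infer that the primary result is compromised. The text does not support that: the intent-to-treat test is set out first, and dose enters only in the further analyses.
- **The size is not known.** A reader might take the simulated figures as bias in the trial's uptake results. The 20 points belong to a primary end point, whereas the between-arm models in question concern mediating outcomes. No planned analysis of 12-month uptake is shown to include dose. Mean dose and the strength of self-selection are assumed.
- **Downstream use is not shown.** It is tempting to say these models drive the optimisation and scale-up conclusions. Implementation Outcomes draws those lessons from scale scores, fidelity measures, interviews and focus groups. The cost-effectiveness section works from costs and the trial's primary end points.
- **Some of this is inference.** The protocol does not write out a model with arm and dose side by side, does not say that its arm coefficient would be reported as the programme effect, and does not state that dose is zero in controls. Provider-level dose may not be zero for controls in the cancer treatment cohort, because both arms are treated at the same hospital.

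These points limit the weight of the concern but do not remove it. By the protocol's own wording the models compare randomised groups, and the covariate is measured during follow-up. Leaving exploratory detail to an SAP is normal, but here a method is stated rather than omitted. A non-zero provider-level dose in some controls does not turn the dose-adjusted arm coefficient into the programme effect.

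**Conclusion.** The concern holds for the further analyses only. An arm coefficient adjusted for participant-level dose is not the programme effect on a mediating outcome, and the dose coefficient is open to self-selection. This rests on reading the dose sentence as applying to the between-arm models just before it, and on the inference that sessions and counselor contacts occur only under ARROW. The arm coefficient could keep all of the effect, lose all of it or change sign, depending on how much of the effect runs through dose and how strongly engagement drives attendance. The documents fix neither. The intent-to-treat conclusions, sample size and power stand. It is worth correcting because the change is small and keeps mechanism findings from appearing to contradict a valid main result.

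**What to change.** 1. Report between-arm effects on mediating outcomes, and the moderation analyses, from models without dose.
2. Examine dose within the ARROW arm only, adjusted for baseline self-efficacy, social support and stigma, which Table 2 already collects. Label the result a non-causal association.
3. If an effect of mechanism or receipt is wanted, specify a formal mediation analysis with its assumptions stated; such a model may legitimately contain both arm and dose. Using the randomised arm as an instrument for session attendance is not clean. ARROW also acts through provider training and care coordination, so a participant who attends no session can still benefit.
4. As a minor wording correction, let the one-on-one dose row in Table 2 count all participants. The row is labelled for AYA living with HIV, and each clinic is to enrol 100 men and 100 females, so women only is evidently not meant.

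The cost is a change of wording and one extra within-arm model, which is less precise because controls are excluded. No new data are needed.
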